## Abstract

**Background:**

Approximately, 8% of community-based adults aged ≥ 50 years in England are frail. Frailty has been found to be associated with poorer outcomes after joint replacement. Targeting frailty preoperatively via exercise and protein supplementation has the potential to improve outcomes for people undergoing joint replacement. Prior to proceeding with a randomised controlled trial (RCT), a feasibility study is necessary to address key uncertainties and explore how to optimise trial design and delivery.

**Methods:**

The Joint PRehabilitation with Exercise and Protein (Joint PREP) study is a feasibility study for a multicentre, two-arm, parallel group, pragmatic, RCT to evaluate the clinical and cost-effectiveness of prehabilitation for frail patients undergoing total hip or knee replacement. Sixty people who are ≥ 65 years of age, frail according to the self-reported Groningen Frailty Indicator, and scheduled to undergo total hip or knee replacement at 2–3 hospitals in England and Wales will be recruited and randomly allocated on a 1:1 ratio to the intervention or usual care group. The usual care group will receive the standard care at their hospital. The intervention group will be given a daily protein supplement and will be asked to follow a home-based, tailored daily exercise programme for 12 weeks before their operation, in addition to usual care. Participants will be supported through six follow-up calls from a physiotherapist during the 12-week intervention period. Study questionnaires will be administered at baseline and 12 weeks after randomisation. Embedded qualitative research with patients will explore their experiences of participating, reasons for nonparticipation, and/or reasons for withdrawal or treatment discontinuation. Primary feasibility outcomes will be eligibility and recruitment rates, adherence to the intervention, and acceptability of the trial and the intervention.

**Discussion:**

This study will generate important data regarding the feasibility of a RCT to evaluate a prehabilitation intervention for frail patients undergoing total hip and knee replacement. A future phase-3 RCT will determine if preoperative exercise and protein supplementation improve the recovery of frail patients after primary joint replacement.

**Trial registration:**

ISRCTN11121506, registered 29 September 2022.

**Supplementary Information:**

The online version contains supplementary material available at 10.1186/s40814-023-01363-6.

## Background

Total hip replacement (THR) and total knee replacement (TKR) are two of the most common elective surgical procedures; in the UK, > 200,000 are performed annually in the National Health Service (NHS) [1, 2]. Joint replacement is performed to provide relief from chronic pain and improve functional ability and is successful for many patients [3]. However, there are a proportion of patients who experience adverse post-operative outcomes, including surgical and medical complications, mortality, chronic postsurgical pain, and long-term functional limitations [4–7]. Research has found that although people with frailty often experience improvements in function and pain with joint replacement, they are particularly susceptible to the risks associated with surgery [8–12]. Frailty is a syndrome, whereby decline in physiological reserve and function confers increased vulnerability to physiological stressors such as surgery.

The prevalence of frailty in community-based adults aged ≥ 50 years in England is estimated to be 8% [13]. Studies from North America show that one-third to one-half of those waiting for a joint replacement are frail [10, 14]. In the UK, the average age of those undergoing THR or TKR is approximately 70 years [1], suggesting that many operations are carried out in frail individuals. Following joint replacement, frailty has been associated with increased mortality, length of hospital stay, admission to intensive care, discharge to institutional care, readmissions, and poorer patient-reported outcomes [8–12]. The prevalence of frailty among patients undergoing joint replacement in the NHS is likely to continue to grow due to the ageing population and increased waiting times for surgery [15].

Frailty is potentially modifiable, and studies suggest it may be treated with interventions including exercise and protein supplementation [16–18]. There is a clinical need and opportunity to determine whether targeting frailty in the preoperative phase via protein supplementation and exercise can improve post-operative outcomes in people undergoing joint replacement. The preoperative phase following a patient being placed on the waiting list for surgery provides a window of opportunity to intervene to ensure that patients undergo operations in an optimised physiological state. However, prior to proceeding with a randomised controlled trial (RCT), a feasibility study is necessary to address key uncertainties regarding whether a RCT is possible and explore how to optimise trial design and delivery.

## Methods

This protocol follows guidance from Standard Protocol Items: Recommendations for Interventional Trials (SPIRIT) [19]. A SPIRIT schedule of enrolment, interventions, and assessment is provided in Table 1, and a SPIRIT checklist is provided in Additional file 1.

**Table 1 Tab1:**
[figure not shown]
SPIRIT schedule of enrolment, interventions, and assessments

^a^Clinical Frailty Scale will be completed by a clinician when the patient attends the hospital for their routine preoperative assessment appointment

^b^Self-efficacy subscale only at 12-week post-randomisation

^c^Intervention group only

^d^Usual care group only

^e^Subsample only

### Aims and objectives

The aim of the study is to estimate the extent to which a full-scale RCT of the clinical and cost-effectiveness of preoperative protein supplementation and structured exercise intervention in frail individuals waiting for a THR or TKR is feasible. Specific objectives are to estimate eligibility, recruitment and retention rates, adherence to and acceptability of the trial, data completion rates, and efficacy potential.

### Design

Joint PRehabilitation with Exercise and Protein (Joint PREP) is a feasibility study for a multicentre, two-arm, parallel group, pragmatic, RCT. The study will be conducted at 2 to 3 NHS elective orthopaedic centres. Embedded qualitative research with patients will explore their motivation to take part and experiences of participating, reasons for nonparticipation, and/or reasons for withdrawal or treatment discontinuation. Group discussions with site staff will elicit views on organisational barriers or facilitators for the RCT and explore positions of equipoise and acceptability of the study. The reporting of this protocol follows the reporting guideline for pilot and feasibility studies [20].

### Regulatory approvals

Ethics approval was obtained from the East of Scotland NHS Research Ethics Committee 2 on 30th August 2022 (reference 22/ES/0033) and Health Research Authority (HRA) approval on 6th September 2022. The study is registered on the International Standard Randomised Controlled Trial Number registry (ISRCTN, reference: ISRCTN11121506). Any protocol amendments will be submitted to the HRA for approval prior to implementation and updated on the ISRCTN registry. All patients will provide informed, written consent prior to study participation.

### Patient and public involvement in study design

This study was designed in collaboration with a patient and public involvement (PPI) group, called the Patient Experience Partnership in Research Group. The group consists of patients with experience of osteoarthritis and joint replacement. Through group meetings, patient representatives have worked with the research team to codesign the intervention and study, including testing protein supplements, providing feedback on the exercise component and documents, preparing patient-facing study documents, and developing the patient interview topic guide. The research team and PPI group will continue to work together during the study to interpret study findings, develop strategies and outputs for public dissemination, and plan a grant application for a RCT if this study demonstrates that a trial is feasible.

### Patient recruitment

An overview of participant flow is provided in Fig. 1.

**Fig. 1 Fig1:**
[figure not shown]
Participant flow

#### Eligibility criteria

Inclusion criteria are patients scheduled for primary THR or TKR, ≥ 12 weeks until intended date of operation, ≥ 65 years of age, and frail according to self-reported Groningen Frailty Indicator (score of ≥ 4) (29). Exclusion criteria include contraindications to following study treatments (e.g. following a low-protein diet or comorbidities which preclude participation in exercise), participating in another study that may affect the outcomes of this feasibility study or that does not permit co-enrollment in another study or where co-enrollment would be burdensome to the patient, or unable or unwilling to provide informed consent.

#### Screening and recruitment

NHS patients on waiting lists for a THR or TKR who are aged ≥ 65 years and within an appropriate window prior to their anticipated date of surgery (i.e. as close to 12 weeks prior to surgery as possible) will be identified by the clinical care team and sent a study information pack and screening questionnaire. The screening questionnaire includes demographic questions, the Groningen Frailty Indicator [21], the self-reported version of the Clinical Frailty Scale [22], and questions about ability to participate in exercise, consume extra protein, and participate in other studies. Interested patients are asked to complete and return the screening questionnaire and consent form in a pre-paid self-addressed envelope. One reminder pack will be sent if no response is received within 1 to 2 weeks, followed by a telephone call to ask if they would like any additional support to participate, such as completing the questionnaire over the telephone. Patients who return a screening questionnaire and consent form and meet the eligibility criteria will then be telephoned by the local research team to confirm that they fully understand what participation involves, answer any questions, and explain what will happen during the study. Participants will then be sent a baseline questionnaire to complete. All patients meeting the eligibility criteria will be invited to consider participation in a telephone/online semi-structured interview.

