### Randomisation

Participants will be randomised by a member of the local research team using a computer-based tool (REDCap), stratified by study site and operation type (THR/TKR), with full allocation concealment. Randomisation will be conducted as soon as possible after the research team receive a completed baseline questionnaire. Participants will be informed of their treatment allocation by letter, followed by a telephone call for participants randomised to the intervention group to discuss arrangements for the intervention. Blinding of study participants will not be possible due to the nature of this intervention. After participants have been randomised, a letter will be sent to their GP to inform them of their participation in the Joint PREP study and their treatment allocation.

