### Intervention

Participants randomised to the intervention arm will undertake 12 weeks of a preoperative exercise and protein supplementation intervention. The intervention was designed as a personalised and home-based programme with regular contact and support to maximise success [23]. An intervention duration of 12 weeks was informed by previous research that at least this duration of exercise is required to have benefits relevant to frailty [18]. Reporting of the intervention follows guidance from the template for intervention description and replication (TIDieR) [24], and a TIDieR checklist is provided in Additional file 2.

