#### Exercise

Participants will have an initial 1:1 appointment with a trained physiotherapist (either in person at the hospital or virtually via a secure video platform) to introduce the intervention and develop a 12-week individualised home-based exercise programme. A risk assessment will be carried out and will inform adaptation of exercises and progression schedule to ensure they are tailored to individual physical capabilities and to minimise risk. Appropriate progressions (difficulty and number of repetitions) will be agreed, and participants will be supported with telephone calls every 2 weeks to gradually increase their levels of moderate physical activity throughout the intervention period. The exercises and resources are based on the NEMEX-TJR programme (https://nemex.trekeducation.org) and have been adapted for home use with permission from the Translating Research Evidence and Knowledge programme at La Trobe University, Australia (https://trekeducation.org). The exercises include a warmup, pelvic lifts, sit-ups, lunges, sideway lunges, knee flexion and extension, hip abduction and adduction, chair stands, step-ups, and a cool down. Participants will be provided with two booklets to assist them with completing the exercises. One booklet will have instructions and illustrations for each of the exercises, and the other will have more general information about maintaining exercise, goal setting, pacing, and how best to deal with setbacks. Participants will also be offered the option of signing up to an online platform to support the home-exercise programme. All participants will be issued with Therabands (of varying resistance) for the knee and hip exercises, and where appropriate, participants will be issued with an exercise step and/or gym ball.

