#### Secondary feasibility outcomes

Completion rates for questionnaires administered at baseline and 12 weeks after randomisation will be calculated. We will estimate the efficacy potential of the intervention using the preoperative WOMAC score at 12 weeks after randomisation. The primary outcome for a future full RCT would be in the post-operative period to reflect that prehabilitation aims to optimise post-operative outcomes. While we are not collecting post-operative patient-reported outcomes in this feasibility study due to our study timelines, preoperative pain and function will give an indication of efficacy potential as they are the strongest predictors of post-operative function and pain after joint replacement [32, 33].

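### The only follow-up WOMAC is treated as preoperative but is fixed at 12 weeks after randomisation, with no rule for participants whose surgery comes first

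*Protocol article*

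**What the plan says.** All references are to the protocol article.

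- **Eligibility criteria** require "≥ 12 weeks until intended date of operation". The point in the process at which this is checked is not given.
- **Screening and recruitment** aims to send the pack "as close to 12 weeks prior to surgery as possible", within what it calls an appropriate window. Non-response is allowed for: "One reminder pack will be sent if no response is received within 1 to 2 weeks", and a telephone call follows. Patients who return the forms and are eligible are telephoned, and "Participants will then be sent a baseline questionnaire to complete".
- **Randomisation**: "Randomisation will be conducted as soon as possible after the research team receive a completed baseline questionnaire". Participants learn their allocation by letter, and those in the intervention group then receive a call about arrangements.
- **Exercise**: "Participants will have an initial 1:1 appointment with a trained physiotherapist", at which the 12-week programme is drawn up. The Intervention section justifies that length on the ground that "at least this duration of exercise is required to have benefits relevant to frailty".
- **Questionnaires and data collection** gives two time points only: baseline, and 12 weeks after randomisation.
- **Secondary feasibility outcomes** estimates efficacy potential from the "preoperative WOMAC score at 12 weeks after randomisation". Statistical analysis has these scores summarised by group and compared descriptively.
- **Primary feasibility outcomes** foresees that an operation may be brought forward and lets adherence be judged against 80% of a shortened period. Nothing comparable is stated for the questionnaire or the WOMAC.

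**The concern.** The plan runs on two clocks. Approach and eligibility are counted back from surgery, while the questionnaire is counted forward from randomisation. Its outcome is preoperative only if at least 12 weeks remain between randomisation and the actual operation, and nothing in the article secures that.

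The article uses the preoperative WOMAC as a stand-in for later benefit because pain and function before surgery predict pain and function after it. A score taken after the joint has been replaced cannot serve that purpose, because it reflects the operation and early recovery. Since there is only one follow-up time point, a participant whose questionnaire falls after surgery has no preoperative follow-up score at all. No later analysis can recover one, so this is a matter of data collection as well as analysis.

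**Working it through.** The plan gives no figure for any of the delays involved, so there is no stated result to reproduce on this point. The check is timeline arithmetic.

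**Inputs from the article**
- Target time of approach: about 12 weeks before surgery (Screening and recruitment).
- Minimum time to the intended operation date: 12 weeks, check point not stated (Eligibility criteria).
- Questionnaire: 12 weeks after randomisation (Questionnaires and data collection).

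**Quantities the article does not give**
- *w* = weeks from sending the pack to surgery.
- *d* = weeks from sending the pack to randomisation.
- *s* = weeks from randomisation to the first physiotherapy appointment.

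**Formulas**
- Weeks left to surgery at randomisation = *w* − *d*.
- Time of the questionnaire relative to surgery = 12 − (*w* − *d*) = 12 + *d* − *w*. A positive value means after surgery.
- The questionnaire is therefore post-operative whenever *w* < 12 + *d*.
- Weeks of programme possible before surgery = *w* − *d* − *s*.

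**Results over assumed values of *d*, with surgery on the intended date** (illustration only)

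| Approach *w* | *d* = 1 | *d* = 2 | *d* = 4 | *d* = 6 |
|---|---|---|---|---|
| 12 weeks | 1 week after | 2 weeks after | 4 weeks after | 6 weeks after |
| 14 weeks | 1 week before | day of surgery | 2 weeks after | 4 weeks after |
| 16 weeks | 3 weeks before | 2 weeks before | day of surgery | 2 weeks after |

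Which cells can occur depends on when the 12-week criterion is checked:

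1. *At identification.* A patient approached at exactly 12 weeks is eligible and has 12 − *d* weeks left at randomisation. Any positive *d* puts the questionnaire after surgery.
2. *When the screening form and consent are returned.* The time already used by the postal return no longer counts against the patient. The eligibility call and the baseline questionnaire still have to be completed. If these take *r* weeks, a patient with exactly 12 weeks at form return has 12 − *r* left, and the questionnaire falls *r* weeks after surgery.
3. *At randomisation.* At least 12 weeks remain to the intended date. At exactly 12 the questionnaire falls at 12 − 12 = 0, the day of surgery. If the operation is then brought forward by *e* weeks, the questionnaire falls *e* weeks after it.

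So the most favourable reading removes the systematic part of the problem but leaves no slack for the earlier operations that the article itself anticipates. Under that same reading a participant at exactly 12 weeks has 12 − *s* weeks for the programme. This is why time available is worth reporting beside adherence.

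**The case against.** The case on the other side has real force, and several parts of it stand.

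- *The 12-week criterion already protects.* The article speaks of meeting the eligibility criteria in connection with patients who have returned their forms. A natural reading is that someone below 12 weeks by then is excluded. The phrase about an appropriate window, read with the 12-week floor, may also allow lead time. Nothing says that the criterion is checked at identification, so the top row of the table should not be taken as the expected case. What remains is that the check point is unstated and that no reading leaves slack.
- *Many operations may be later.* The final physiotherapy call covers carrying on with exercise until surgery where that applies, and hospital data are extracted only if surgery falls within the study period. Both suggest that surgery will often come well after the programme. This stands, and it is why no size can be given.
- *The label excludes post-operative scores.* The comparison is of preoperative scores, and the article says that post-operative patient-reported outcomes are not collected. That may keep such scores out of the summary, but the participant then has no follow-up score at all.
- *Detail of this kind belongs in the full protocol or analysis plan.* Visit windows often do. A change in when the only follow-up form is sent is different, because data not collected before surgery cannot be supplied later.

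A reader might also object that the questionnaire comes too early for the intervention arm, since the programme starts after randomisation. Anchoring follow-up to randomisation gives both arms the same time point and is ordinary in a pragmatic trial, so this is a matter of preference and not an error. The fix below would not change it.

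**Conclusion.** The point holds in a limited form. As written, any participant operated on within 12 weeks of randomisation would provide a post-operative WOMAC or no preoperative follow-up score. The article foresees early operations and adapts only the adherence definition to them.

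The number affected cannot be computed: the delays before randomisation, the check point for the 12-week criterion and the actual surgery dates are not given. The table shows direction and mechanism under assumed delays. It is not an estimate for this study.

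Three stronger conclusions might be inferred and are not supported:

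- That questionnaires will typically fall some weeks after surgery. This needs both an assumed delay and a check at identification, and the article states neither.
- That the 80% provision for shortened programmes will become the usual route to adherence. The article presents an earlier operation only as an example, and 10 of 12 weeks is 83%, so the two rules are of similar proportional stringency.
- That the feasibility decision is compromised through the WOMAC. Efficacy potential is a secondary outcome, compared descriptively in a study not powered for group differences, and progression rests on recruitment, retention and adherence.

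This should be fixed, but it does not threaten the study's main purpose.

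**What to change.** 1. In both arms, collect the follow-up questionnaire at 12 weeks after randomisation or just before surgery, whichever comes first.
2. State that any WOMAC completed after surgery is excluded from the preoperative comparison.
3. State that the existing 12-week criterion is applied at randomisation, and set the identification window so that the enrolment steps fit ahead of it.
4. Report, alongside adherence, the proportion of the intervention arm who had the full 12 weeks available before surgery.

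The following sections must be reconciled on timing: Eligibility criteria, Screening and recruitment, Intervention, Protein, Questionnaires and data collection, Primary feasibility outcomes and Secondary feasibility outcomes.

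The cost is an amendment to the questionnaire trigger and the identification window. No extra visits are needed, but the local team must use the surgery date to time the questionnaire. The downside is some variation in follow-up time, which can be described by arm. Applying the criterion at randomisation may also exclude some patients whose time runs below 12 weeks during enrolment; these should be counted in the screening and recruitment records.
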